### Data Analysis

Demographic and outcome data will be summarized for the whole sample and for each group using mean and standard deviation or median and interquartile range for continuous variables and via frequencies and percentages for categorical ones. For the CH group only a descriptive characterization of the measured variables will be performed. In the CA and EOT groups, baseline data will be compared using t-test or Mann-Whitney U test for continuous variables and with chi-square test and Fisher test for categorical ones. For each group, within group pre-post differences will be computed using t-test for dependent samples or Wilcoxon rank sum test. Linear models will be computed in order to compare outcome data between groups, adjusting by baseline outcome data and also by the variables that showed baseline differences.

Further, the association between olfactory level measured with TDI score and marked OE protein modifications (based on fold-change), cognitive, neurological, functional, mood status and quality of life will be analyzed using Pearson or Spearman correlation coefficients. All significant, nearly significant, clinically relevant or potentially confounding variables will be considered in a multiple linear regression model with TDI as dependent variable. In this global model non-significant variables will be removed, which, when eliminated, do not change the estimators of the effect of the rest of the variables in the model. The biochemical analysis, the immune information of each subject and the data associated with pharmacological treatments, fragility, cognition, will also be correlated with olfactory level, with the aim of testing the precision olfactory medicine as a useful tool in the day-to-day context of the Geriatrics Unit. To exclude the effect of sex and age, correlations will be performed as partial correlations, including sex and age as covariates. The statistical analysis will be performed with SPSS (version 26; SPSS Inc., Chicago, IL, United States).

Sample size was calculated based on previous literature (Hummel et al., 2009) on the effects of OT on olfactory function, a medium effect size (*d* = 0.5) and a standard deviation of the outcome of *SD* = 0.8 were assumed (Birte-Antina et al., 2018).

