Therefore, although the protocol proposed follows the main guidelines of the protocols founded in the literature, our target sample is older than the previously studied and, the training protocol proposed presents possible improvements in terms of simplicity, follow-up and adherence comparing to the existent evidence. In addition, the expected sensorial improvement will be accompanied by unprecedented personalized OE proteotypes (composed around quantitative data from 4500 to 5000 proteins) that will help us to understand the unknown molecular mechanisms triggered by the OT. Moreover, this workflow has the capacity to unveil protein mediators that may be targeted by future therapies in order to improve the odor capacity and the olfactory recovery.

Research in the field of immunology, as well as in various neurological disorders, indicate the increasing relevance of smell. In this study, we pretend to implement olfactory precision medicine through immunodulatory nasal therapies, so the results obtained from immune populations, before and after OT, could shed a light on the brain-smell-immune system axis.

To sum-up our hypothesis indicates that the structured, short-term exposure to odors may increase olfactory sensitivity (Hummel et al., 2009). However, the magnitude of this effect and its causality are still unknown in the elderly population. Following the literature, the main management strategies for age-related olfactory dysfunction are odor stimulation (Yokoyama et al., 2011; Kondo et al., 2020), OT (Schriever et al., 2014) and exercise regularly (Schubert et al., 2013).

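### The regression on TDI picks its predictors by significance and tests them in the same participants (at most 120 where proteins are involved), so its p-values and R-squared will look better than they are

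*Protocol article*

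**What the plan says.** The Data Analysis section of the protocol article sets out a sequence for relating olfactory level to other variables.

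- **Correlation step.** The association of TDI with "marked OE protein modifications (based on fold-change), cognitive, neurological, functional, mood status and quality of life will be analyzed using Pearson or Spearman correlation coefficients".
- **Entry rule.** "All significant, nearly significant, clinically relevant or potentially confounding variables will be considered in a multiple linear regression model with TDI as dependent variable". No limit is given for the second of these categories.
- **Removal rule.** "In this global model non-significant variables will be removed", but with a condition attached: a term leaves only if it is non-significant and dropping it does not alter the estimates for the terms that stay. The size of change that counts is not given.
- **Further correlations.** After the model rule the section adds: "The biochemical analysis, the immune information of each subject and the data associated with pharmacological treatments, fragility, cognition, will also be correlated with olfactory level". It does not say that these variables enter the regression.
- **Adjustment.** To exclude the effect of sex and age, "correlations will be performed as partial correlations, including sex and age as covariates".

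Two other places set the scale. The Outcomes section restricts the comparative protein analysis to the EOT and CA groups, and Expected Results describes "quantitative data from 4500 to 5000 proteins". The Data Analysis section gives no cut-off for a marked fold-change and does not say how many proteins will pass.

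**The concern.** Variables reach the regression partly because they correlated with TDI in this sample, and they are then tested against TDI in the same sample. A predictor that passed such a screen by chance tends to look significant again, because its estimate carries the same chance deviation. The final p-values, coefficients and R-squared do not allow for the selection.

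The protein step adds a separate weakness. A fold-change takes no account of each protein's variance, so a marked change can be a noisy one, and the filter carries no error rate.

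The section gives the aim of this work as testing olfactory precision medicine as a useful tool in daily geriatric practice, and Expected Results hopes that the proteomic workflow will reveal protein mediators for future therapies. Predictors that arise from noise would be a poor basis for either.

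**Working it through.** **Inputs from the article.** 60 people each in EOT and CA, hence 60 + 60 = 120 at most with proteomics (Study Design and Participants; Outcomes). The CH group is described only (Data Analysis). 4,500 to 5,000 proteins are quantified (Expected Results). The article states no error rate or expected yield for this model, so there is no figure of its own to reproduce.

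**Assumed.** Nearly significant means p < 0.10. A term is significant at p < 0.05. The change-in-estimate limit is 10%. Candidates are independent and unrelated to TDI. The number of candidates m is varied, because the article does not fix it.

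**Step 1: the screen alone.** Expected false hits are m × α, and the chance of at least one is 1 − (1 − α)^m.

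- m = 20: 20 × 0.05 = 1.0; 1 − 0.95^20 = 0.64
- m = 30: 30 × 0.05 = 1.5 (30 × 0.10 = 3 at the wider limit); 1 − 0.95^30 = 0.79
- m = 100: 100 × 0.05 = 5 (100 × 0.10 = 10); 1 − 0.95^100 = 0.994

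**Step 2: the whole rule, by simulation.** 200 null data sets per setting, n = 120: screen at p < 0.10, enter all that pass, remove terms with p > 0.05. This was done first on the p-value alone, then with the 10% change-in-estimate condition added. Each cell gives the mean number of significant predictors left, the share of runs with at least one, and the mean R-squared.

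| Candidates | p-value removal only | With change-in-estimate condition |
|---|---|---|
| 30 | 1.6; 80%; 0.07 | 1.6; 79%; 0.09 |
| 50 | 2.6; 93%; 0.12 | 2.1; 89%; 0.14 |
| 100 | 4.9; 99%; 0.22 | 3.7; 97%; 0.27 |
| 200 | 9.1; 100%; 0.38 | 6.0; 99%; 0.48 |

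The Monte Carlo standard error of the 80% is √(0.8 × 0.2 / 200) = 0.028. With the extra condition fewer terms are significant at 50 or more candidates, but R-squared rises because non-significant terms stay in.

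**Step 3: a benchmark for R-squared.** With k noise predictors chosen without looking at the data, the expected R-squared is k/(n − 1). For k = 1.6 this is 1.6/119 = 0.013, against 0.07 after selection. For k = 4.9 it is 4.9/119 = 0.041, against 0.22. Selection inflates it about fivefold in both cases.

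**Step 4: the upper bound for proteins.** If every quantified protein were tested at p < 0.05 and none were related to TDI, false hits would number 4,500 × 0.05 = 225 to 5,000 × 0.05 = 250. Only proteins marked by fold-change go to correlation and their number is not given, so this is a ceiling and not a forecast.

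**Step 5: sex and age.** The simulation used simple correlations. Partial correlations on two covariates control confounding by sex and age. They leave the false-positive rate of each test at its nominal level, so they do not reduce the number of false hits.

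**The case against.** Much can be said for the plan.

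- **The rule is not pure stepwise selection on p-values.** Removal also requires stable estimates, and clinically relevant or confounding variables may enter whatever their p-value. This is correct and the rule should be described so. The simulation shows that the added condition does not remove the problem.
- **A reader might infer that the plan will produce 225 to 250 false protein findings.** The document does not support this. It correlates only fold-change-marked proteins. Nor does it say that fold-change is computed against TDI, so that filter need not itself select on the outcome. The double use of the data lies in the step from correlation to regression.
- **A reader might infer that immune, biochemical and drug data feed the regression.** The text says only that they are correlated with olfactory level.
- **A reader might infer that no multiplicity control exists.** This is a condensed article that refers the proteomic methods to earlier work, and control of the false-discovery rate may stand in documents not shown. Its absence here is therefore not the point. The point is the selection rule that the article does state.
- **Independence is generous to the criticism.** MMSE, TMT-A and SDMT are related, as are SPPB, Barthel and handgrip. Positive correlation lowers the chance of at least one false hit. This stands, and the percentages should be read with it in mind.
- **The analysis is secondary, in a study whose Introduction calls it a pilot.** This stands and limits the weight of the point.

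**Conclusion.** The concern holds for the stated entry and removal rule. Selecting on significance and then testing in the same people (at most 120 where proteins are involved) makes the final p-values too small and inflates coefficients and R-squared. On pure noise, 30 candidates give at least one significant predictor in about 80% of runs with R-squared 0.07 to 0.09; 100 candidates give about 4 to 5 predictors with R-squared 0.22 to 0.27. These figures rest on the assumed entry limit of p < 0.10, the assumed 10% change limit and independent candidates. Correlated clinical measures would lower the chance of at least one. The true number of candidates is unknown, because the article leaves both the fold-change cut-off and the limit for nearly significant open.

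Two stronger conclusions are not supported. The primary comparison of TDI between EOT and CA uses a separate linear model adjusted for baseline and is not affected. Nor can it be said that false leads will be the main product of the study: this is a secondary association analysis, and the article's words on protein mediators concern what the proteomic workflow might reveal.

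**What to change.** 1. Replace the significance-based entry and removal rule. Either fix a short list of predictors in advance, including group, age and sex, keep all of them whatever their p-values and report confidence intervals; or use a penalised regression and report an internally validated R-squared.
2. Choose proteins by a per-protein model with Benjamini-Hochberg control of the false-discovery rate. Keep fold-change only as an additional filter, with its cut-off stated.
3. State whether the immune, biochemical and drug variables are candidates for the regression or are only correlated with TDI.
4. Label these analyses exploratory.

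The cost is analysis work only: no new data, visits or participants. The downside is that fewer proteins and predictors will be reported as findings.

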## Abstract

The aim of this article is to present the research protocol for a prospective cohort study that will assess the olfactory function and the effect of an intervention based on olfactory training in healthy very old adults (≥75 years old). A convenience sample of 180 older people (50% female) will be recruited in three different environments: hospitalized control group (CH) with stable acute illness (*n* = 60); ambulatory control group (CA) of community-based living (*n* = 60); and an experimental odor training group (EOT) from nursing homes (*n* = 60). The odor training (OT) intervention will last 12 weeks. All the volunteers will be assessed at baseline; CA and EOT groups will also be assessed after 12 weeks. The primary end point will be change in olfactory capacity from baseline to 12 weeks period of intervention or control. The intervention effects will be assessed with the overall score achieved in Sniffin Sticks Test (SST) – Threshold, Discrimination, and Identification (TDI) extended version. Secondary end points will be changes in cognitive tasks, quality of life, mood, immune status, and functional capacity. All these measurements will be complemented with an immune fitness characterization and a deep proteome profiling of the olfactory epithelium (OE) cultured *ex vivo*. The current study will provide additional evidence to support the implementation of olfactory precision medicine and the development of immunomodulatory nasal therapies based on non-invasive procedures. The proposed intervention will also intend to increase the knowledge about the olfactory function in very elderly people, improve function and quality of life, and promote the recovery of the health.

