## Materials and Methods

### Study Design and Participants

The sample is a convenience sample and is composed by three groups (*N* = 180, 50% females). Sixty hospitalized patients with acute illness (hospitalized control group – CH), sixty ambulatory patients from the community (ambulatory control group – CA) and, sixty from nursing home – the experimental odor training group (EOT). The study follow the principles of the Declaration of Helsinki (World Medical Association, 2013) and was approved by the Complejo Hospitalario de Navarra Clinical Research Ethics Committee on October 21, 2020 (PI_2020/113). All volunteers or their legal representatives will be asked to sign a written informed consent form, also approved in advance by the ethics committee. There will be no financial compensation.

Following the literature procedures (Delgado-Losada et al., 2020) all the volunteers will be previously evaluated by an expert otolaryngologist including anamnesis and nasal endoscopic examination to exclude the possibility of an otorhinolaryngology alteration or pathology that may modify the results of the olfactory test. Therefore, sinusitis, prior nasal surgery, nasal polyps, presence of nasal congestion at the moment of test administration or recent upper respiratory tract infection within two weeks, medication intake with repercussion in olfactory performance or to have reported COVID-19 compatible smell symptomatology are exclusion criteria.

The inclusion criteria are: (i) ≥ 75 years old; (ii) compliance with testing procedure; (iii) Mini-Mental State Examination (MMSE) equal to or greater than 21 points (Pi et al., 1994; Ostrosky-Solís et al., 2000; Reyes-de-Beaman et al., 2004); (iv) Barthel index ≥ 60; (v) participants from acute hospitalized group must be clinically stable. The exclusion criteria are positive diagnosis of any kind of neurodegenerative disease and/or nasosinusal pathology (described before).

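### The TDI correlations adjust for sex and age but not study group, so if CA and EOT are pooled, differences between settings can produce correlations that exist in neither setting

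*Protocol article*

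**What the plan says.** The Data Analysis section describes two sets of correlations with TDI. The first covers olfactory epithelium protein changes and clinical measures: "cognitive, neurological, functional, mood status and quality of life will be analyzed using Pearson or Spearman correlation coefficients". The second is broader: "The biochemical analysis, the immune information of each subject and the data associated with pharmacological treatments, fragility, cognition, will also be correlated with olfactory level". The article ties this second set to the aim of testing olfactory precision medicine as a practical tool in the Geriatrics Unit. The adjustment is then stated: "To exclude the effect of sex and age, correlations will be performed as partial correlations, including sex and age as covariates".

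No correlation is described as within-group, stratified or adjusted for group. The section does not say which groups or which time point enter.

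Three other statements bear on the point:
- Study Design and Participants: "The sample is a convenience sample and is composed by three groups", namely "Sixty hospitalized patients with acute illness (hospitalized control group – CH), sixty ambulatory patients from the community" (CA), and sixty nursing-home residents (EOT). Under Intervention, EOT is trained and CA is not.
- Data Analysis restricts the CH group to descriptive characterization.
- Data Analysis also plans a regression: "All significant, nearly significant, clinically relevant or potentially confounding variables will be considered in a multiple linear regression model with TDI as dependent variable". A non-significant variable is removed only if its removal leaves the other estimates unchanged. Group is not named as a candidate.

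**The concern.** In this study, group and setting are the same thing. People in a nursing home and people living in the community may differ in function, comorbidity, drug treatment and immune status, and also in smell. Where both variables in a pair differ by setting, a pooled correlation mixes the within-setting association with the difference between the two group means. Sex and age remove only the part of that difference which they explain.

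The plan already foresees baseline imbalance between CA and EOT. It tests for it and adjusts the between-group linear models for the variables that differ. That protection is not carried over to the correlations. At stake is whether a correlation offered in support of a clinical use of smell testing describes a link between smell and health, or partly describes where people were recruited.

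**Working it through.** **Inputs from the article.** 60 per group; CA and EOT pooled gives n = 120; covariates are sex and age. The article gives no target, sample size or power for the correlations, so there is no figure of its own to reproduce.

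**Assumption.** The article gives no between-setting differences. Let s be the shift between CA and EOT, in within-group SDs after allowing for sex and age, taken as equal for TDI and for the other measure. Let the true within-group correlation be zero.

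**Expected correlation.** For two equal groups whose means differ by s, the between-group variance is s²/4. The shift is shared, so the covariance is also s²/4, and each total variance is 1 + s²/4. Hence

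r = (s²/4) / (1 + s²/4)

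- s = 0.3: 0.0225 / 1.0225 = 0.022
- s = 0.5: 0.0625 / 1.0625 = 0.059
- s = 0.8: 0.16 / 1.16 = 0.138
- s = 1.0: 0.25 / 1.25 = 0.200

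**False-positive rate.** This was simulated with 4,000 replicates per case and 60 per group. Age and sex affected both variables, and the Pearson partial correlation was tested at two-sided 5%.

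| s (both variables) | Mean r, sex and age only | Rejections, sex and age only | Mean r, group added | Rejections, group added |
|---|---|---|---|---|
| 0 | 0.00 | 4.5% | 0.00 | 4.6% |
| 0.3 | 0.02 | 5.3% | 0.00 | 4.5% |
| 0.5 | 0.06 | 10.0% | 0.00 | 5.0% |
| 0.8 | 0.14 | 32.7% | 0.00 | 5.3% |
| 1.0 | 0.20 | 59.8% | 0.00 | 4.8% |

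The simulated mean r agrees with the formula. A separate simulation with 6,000 replicates and no covariates gave 10%, 32% and 61% at 0.5, 0.8 and 1.0 SD.

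**Two boundary checks.**
- Age does not stand in for group. With an age gap of 0.5 SD between the groups and s = 0.5, rejections are 8.9% with sex and age, and 4.2% once group is added.
- Both variables must differ. If only TDI is shifted (0.8 SD), rejections are 5.0%, so there is no inflation.

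**The case against.** The strongest reply has four parts.

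**Pooling and time point are inferred.** The article does not say in terms that groups are pooled, and a condensed article may leave the analysis set to the full plan. This stands as a qualification. But the covariate list is stated, no by-group wording appears, and the reference to "the immune information of each subject and the data associated with pharmacological treatments, fragility, cognition, will also be correlated with olfactory level" reads more naturally as one pooled analysis than as separate ones.

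**The regression may deal with it.** It admits potentially confounding variables, and its removal rule would keep group wherever dropping it changed the other estimates. That is a real safeguard if group is entered. However, group is not named, and for the immune, biochemical and drug-treatment data the article describes correlations only.

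**The settings may differ little.** All participants must have MMSE of at least 21 and Barthel of at least 60, with no neurodegenerative or nasosinusal disease. These criteria narrow the contrast, and at 0.3 SD there is practically no inflation. This stands, and it is why the result is conditional.

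**Adjusting for group changes the question.** The estimate becomes a within-setting association. If setting is partly a consequence of function or cognition, some real variation between people is removed. This is a fair cost, and a reason to show both results.

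Three stronger readings are tempting, but the documents do not support them. A reader might infer that these correlations will be artefacts of recruitment; nothing in the article shows that both variables differ by setting, and the calculation assumes no true association. A reader might extend the figures to three pooled groups because participants are "recruited in three different environments"; the descriptive-only statement for CH speaks against that. A reader might add that training worsens the bias at 12 weeks; a shift in TDI alone creates no correlation, and training could narrow a gap as well as widen one.

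**Conclusion.** The point holds in conditional form. As stated, the partial correlations leave any CA-to-EOT difference not explained by sex and age in the estimate. With zero within-setting association and n = 120, the false-positive rate stays near 5% at a shared shift of 0.3 SD. It rises to about 10% at 0.5 SD, 32% at 0.8 SD and 60% at 1.0 SD.

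This rests on three assumptions: CA and EOT are pooled, both variables differ by setting beyond sex and age, and the shifts are equal in the two variables. None of the shifts comes from the article. The weakness concerns secondary associations. The comparison of TDI between groups has its own adjustment and is untouched. The change is worth making because a stated aim depends on some of these correlations and the remedy is simple.

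**What to change.** 1. Add study group to sex and age as a covariate in every pooled partial correlation, or report within-group correlations and combine them. The sex-and-age-only result can be shown alongside for transparency.
2. Name study group as a confounder to be entered in the multiple regression with TDI as dependent variable.
3. State which groups and which time point enter. Use baseline values for cross-sectional associations, and analyse change against change within EOT and CA separately.

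The cost is one degree of freedom in the two-group case (from 120 − 2 − 2 = 116 to 115), a small change in the analysis code and no new data. The adjusted correlation must be described as a within-setting association, and it may lose some real between-setting variation.
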